## Abstract

**Background:**

There is a strong rational of using anti–programmed cell death protein-1 and its ligand (anti–PD-1/L1) antibodies in human papillomavirus (HPV)–induced cancers. However, anti–PD-1/L1 as monotherapy induces a limited number of objective responses. The development of novel combinations in order to improve the clinical efficacy of an anti–PD-1/L1 is therefore of interest. Combining anti–PD-1/L1 therapy with an antitumor vaccine seems promising in HPV-positive (+) cancers. UCPVax is a therapeutic cancer vaccine composed of two separate peptides derived from telomerase (hTERT, human telomerase reverse transcriptase). UCPVax is being evaluated in a multicenter phase I/II study in NSCLC (non–small cell lung cancer) and has demonstrated to be safe and immunogenic. The aim of the VolATIL study is to evaluate the combination of atezolizumab (an anti-PD-L1) and UCPVax vaccine in a multicenter phase II study in patients with HPV^+^ cancers.

**Methods:**

Patients with HPV^+^ cancer (anal canal, head and neck, and cervical or vulvar), at locally advanced or metastatic stage, and refractory to at least one line of systemic chemotherapy are eligible. The primary end point is the objective response rate (ORR) at 4 months. Patients will receive atezolizumab every 3 weeks at a fixed dose of 1,200 mg in combination with the UCPVax vaccine at 1 mg subcutaneously.

**Discussion:**

Anti-cancer vaccines can restore cancer-immunity *via* the expansion and activation of tumor-specific T cells in patients lacking pre-existing anti-tumor responses. Moreover, preclinical data showed that specific T_H_1 CD4 T cells sustain the quality and homing of an antigen-specific CD8^+^ T-cell immunity. In previous clinical studies, the induction of anti-hTERT immunity was significantly correlated to survival in patients with advanced squamous anal cell carcinoma. Thus, there is a strong rational to combine an anti-cancer hTERT vaccine and an immune checkpoint inhibitor to activate and promote antitumor T-cell immunity. This pivotal proof of concept study will evaluate the efficacy and safety of the combination of a telomerase-based T_H_1 inducing vaccine (UCPVax) and an anti–PD-L1 (atezolizumab) immunotherapy in HPV^+^ cancers, as well as confirming their synergic mechanism, and settling the basis for a new combination for future clinical trials.

**Clinical Trial Registration:**

https://www.clinicaltrials.gov/, identifier NCT03946358.

## 1 Introduction

More than 90% of anal and cervical cancers and about 70% of oropharyngeal cancers are linked to the human papillomavirus (HPV) infection (1, 2), and their incidence is steadily increasing (3, 4). HPV oncogenic proteins are trans-activators of telomerase (5). Telomerase is an enzyme that is re-expressed in most tumor cells and it ensures the reconstitution of the telomeres, which are shortened at each cell division and prevents the entry of the cell in replicative senescence. This enzyme is composed of a catalytic subunit, human telomerase reverse transcriptase (hTERT) and a structural subunit composed of a telomerase RNA component (TERC). The main mechanism of telomere maintenance in cancers depends on the reactivation of hTERT, which is overexpressed in more than 90% of human cancers, thus conferring to cancer cells a form of immortality (6).

This overexpression of telomerase in tumor cells compared with normal cells confers to hTERT the property of a tumor antigen. Our group has conducted a clinical trial (Epitopes-HPV01 and Epitopes-HPV02) in advanced squamous cell anal cancer where a correlation was evidenced between the presence of anti-HPV immunity and anti-telomerase T_H_1 CD4 T-cell responses. We could unwaveringly establish that telomerase is an appropriate antigen in HPV-related cancers (7, 8).

Besides, tumor-reactive CD4^+^ T cells have been found to ensure efficient effector cytolytic T lymphocytes (CTLs) recruitment at the tumor site (9, 10). In consequence, the promotion of tumor specific T_H_1 CD4 activation might be an attractive therapeutic option to enhance anti–programmed cell death protein-1 and its ligand (anti–PD-1/L1) efficacy (11). However, no option is currently available to expand tumor specific T_H_1 lymphocytes in most patients. We have used an optimized reverse immunology approach to identify four novel MHC class II–restricted peptides derived from hTERT referred as “Universal Cancer Peptides” (UCP). UCPVax is a therapeutic cancer vaccine composed of two separate peptides called UCP2 and UCP4 derived from telomerase (12). This UCPVax vaccine is currently being evaluated in a multicenter phase I/II study in NSCLC (NCT2818426). Results from the phase I study indicated that UCPVax was safe, well tolerated, and immunogenic at the doses and schedule tested, and 1 mg of each peptide was recommended for phase II. UCPVax was immunogenic in 60% of NSCLC patients at least after three injections, with preliminary signals of clinical efficacy in this population. Accordingly, we selected this 1-mg dose of each peptide in the VolATIL study.

Preclinical and clinical data demonstrated PD-1/L1 immune checkpoint as a relevant target for immunotherapy in HPV^+^ cancers, based on the prominent role of PD-1 and PD-L1 in HPV-driven immune evasion. The role of PD-L1 in immune evasion of HPV-associated tumors was well described in head and neck squamous cell carcinoma (HNSCC). A membranous expression of PD-L1 on epithelial cells and macrophages was observed in tonsillar crypts of HPV-infected patients. Similarly, the majority of CD8^+^ T lymphocytes of these patients expressed high levels of PD-L1 (13–15). In mice, PD-1 neutralization synergized with HPV vaccine to promote an anti-tumor immunity (16).

Recent clinical trials also confirmed the interest of PD-1/L1 inhibitors in HPV^+^ cancers. In patients with advanced squamous cell carcinoma of the anus (SCCA), refractory to at least one line of treatment, five prospective phase I/II trials included 298 patients (11, 17–21). ORR was 13.4% including the 3.7% of complete responses. The median overall survival (OS) was approximately 11 months (**Table 1**). In cervical cancer patients with PD-L1–positive advanced disease and refractory to at least one systemic treatment, pembrolizumab induced an ORR in 15 of 101 (14.9%) patients including two (2%) complete responses in two prospective trials (22, 23). In HNSCC, the strongest available data for checkpoint inhibitors in refractory disease come from an initial and expansion cohort of a phase Ib study using pembrolizumab in the recurrent/metastatic setting. Among 192 patients enrolled, 18% presented an objective response including four complete responses (24).

**Table 1 T1:** PD1/L-1 treatment in patients with refractory-advanced squamous cell carcinoma of the anus.

Treatment(Reference)	Nivolumab (15)	Pembrolizumab (16, 17)	Retifanlimab (18)	Avelumab (19)
Number of patients	37	137	94	30
Objective response: N (%)	9 (24.3)	15 (10.9)	13 (13.8)	3 (10.0)
Complete response: N (%)	2 (5.4)	8 (5.8)	1 (1.1)	0
mPFS (months)	4.1	2.1	2.3	2.0
mOS (months)	11.5	11.7	10.1	13.9

Even though anti–PD-1/L1 therapies in HPV^+^ cancers are effective, the benefit is limited to approximately 15% of patients in monotherapy, and only a few patients achieved a long-term remission. Therefore, the development of a novel combination in order to extend the clinical efficacy of anti–PD-1/L1 is of great interest.

Altogether, the combination of anti–PD-1/L1 therapy with an antitumor vaccine gains serious consideration in HPV^+^ cancers. In the present VolATIL clinical trial, we will evaluate the clinical interest and immunological efficacy of a treatment combining the UCPVax with anti–PD-L1 therapy (atezolizumab) in patients with HPV^+^ cancers (anal canal, cervix and vulvar, and oropharyngeal cancers) by evaluation of the objective response rate (ORR) at 4 months according to iRECIST criteria. We will also explore, as a secondary objective, the feasibility of specific tumor-infiltrating lymphocytes (TIL) production.

## 2 Methods and Analysis

### 2.1 Design

VolATIL study is a multicenter phase II trial to evaluate the combination of atezolizumab and UCPVax in advanced HPV^+^ cancer patients, refractory to at least one line of systemic chemotherapy. The study was developed by the “National Institute of Health and Medical Research (INSERM), Unit 1098” and “Clinical Investigational Center (CIC) 1431”. The study is sponsored by the CHU of Besançon and supported by INCa (French National Cancer Institute) and ROCHE. The data management is undertaken by the “Methodology and Quality of Life Unit in Oncology”* from the University Hospital of Besançon. The trial is registered on the clinicaltrials.gov database (NCT03946358).

The study has received a favorable opinion from the Ethic Committee “Sud-Est IV” and the authorization from the French National Agency for the Safety of Medicines and Health Products and will be conducted in accordance with the Declaration of Helsinki and the Good Clinical Practice.

* http://www.umqvc.org/en/index.html

### 2.2 Study Objectives

The main objective of this clinical trial is to assess the efficacy of the strategy combining UCPVax and atezolizumab in patients with advanced refractory HPV^+^ cancer by evaluation of the ORR at 4 months according to iRECIST.

The secondary objectives are the following:

OSProgression-free survival (PFS)Health-related quality of life (QoL)Safety of atezolizumab in combination with UCPVaxAbility of UCPVax and atezolizumab to promote the activity of antigen specific T lymphocytes in the peripheral bloodAbility of UCPVax and atezolizumab to enhance the tumor cell infiltration by specific lymphocytes (tumor-infiltrating lymphocytes, TIL)Feasibility of TIL expansion in HPV^+^ cancer patientsResearch of biomarkers

### 2.3 Patient Selection

The study population consists of patients with HPV^+^ (defined by p16^+^ by immunohistochemistry or HPV genotyping) cancer, locally advanced or metastatic, and refractory to systemic chemotherapy, corresponding to one of the following selected types:

Carcinoma of the anusCarcinoma of the head and neckCarcinoma of the cervix or vulva

Patients should have an ECOG-PS <2 and adequate organ function.

The main inclusion and exclusion criteria are listed in **Table 2**.

**Table 2 T2:** Main inclusion and exclusion criteria.

** *Inclusion criteria* ** ➢ Histologically confirmed HPV^+^ cancers, defined by p16^+^ (IHC) or HPV genotyping (HPV genotyping mandatory for non-squamous and adenocarcinoma, because p16 is not validated as a surrogate marker), corresponding to one of the following selected types: –Carcinoma of the anus –Carcinoma of head and neck –Carcinoma of cervix or vulva ➢ Locally advanced or metastatic disease ➢ Patient treated by a first line of anti-cancer standard treatment performed in advanced or metastatic disease ➢ Age ≥18 and ≤75 years old ➢ ECOG-PS <2 ➢ Signed written informed consent ** *Exclusion Criteria* ** Non-eligible to a clinical trial: ➢Patients previously exposed to anti-tumor immunotherapy as anti–PD-1, anti–PD-L1, or anti-CTLA4 agent or any immune therapy (HPV vaccination is allowed) ➢Diagnosis of additional malignancy within 3 years prior to the inclusion with the exception of curatively treated basal cell carcinoma of the skin and/or curatively resected *in situ* cervical or breast cancer ➢Patient with any medical or psychiatric condition or disease, which would make the patient inappropriate for entry into this study ➢Current participation in a study of an investigational agent or in the period of exclusion ➢Patient under guardianship, curatorship, or under the protection of justice Cancer-specific exclusion criteria: ➢Uncontrolled pleural effusion, pericardial effusion, ascites, or symptomatic fistula ➢Uncontrolled tumor-related pain: exposing patients to risk of exposure to corticoids or iterative hospitalizations. Symptomatic lesions amenable to palliative radiotherapy should be treated prior to inclusion. Patients should be recovered from the effects of radiation. There is no required minimum recovery period ➢Known active central nervous system metastases and/or carcinomatous meningitis. Subject with previously treated brain metastases and with radiological and clinical stability are allowed Non-eligible to treatment: ➢Inadequate organ functions: known cardiac failure of unstable coronaropathy, respiratory failure, or uncontrolled infection or another life-risk condition ➢Active or chronic hepatitis B or C and/or HIV-positive (HIV 1/2 antibodies patients), or a known history of active Tuberculosis bacillus ➢Any immunosuppressive therapy (i.e., corticosteroids >10 mg of hydrocortisone or equivalent dose) within 14 days before the planned start of study therapy ➢Active autoimmune disease that has required a systemic treatment in the past 2 years (i.e., corticosteroids or immunosuppressive drugs). Replacement therapy (e.g., thyroxine and insulin) is allowed ➢Active or history of autoimmune disease or immune deficiency, including, but not limited to, myasthenia gravis, myositis, autoimmune hepatitis, systemic lupus erythematosus, rheumatoid arthritis, inflammatory bowel disease, antiphospholipid antibody syndrome, Wegener granulomatosis, Sjögren syndrome, Guillain–Barré syndrome, or multiple sclerosis (see Annex 5 for a more comprehensive list of autoimmune diseases and immune deficiencies) with the following exceptions: ➢Patients with a history of autoimmune-related hypothyroidism who are on thyroid replacement hormone are eligible for the study ➢Patients with controlled type 1 diabetes mellitus who are on an insulin regimen are eligible for the study ➢Patients with eczema, psoriasis, lichen simplex chronicus, or vitiligo with dermatologic manifestations only (e.g., patients with psoriatic arthritis are excluded) are eligible for the study provided that all of following conditions are met: - Rash must cover ≥10% of body surface area - Disease is well controlled at baseline and requires only low-potency topical corticosteroids - No occurrence of acute exacerbations of the underlying condition requiring psoralen plus ultraviolet A radiation, methotrexate, retinoids, biologic agents, oral calcineurin inhibitors, or high potency or oral corticosteroids within the previous 12 months ➢Prior allogeneic bone marrow transplantation or prior solid organ transplantation ➢History of severe allergic, anaphylactic, or other hypersensitivity reactions to chimeric or humanized antibodies or fusion proteins ➢Known hypersensitivity or allergy to Chinese hamster ovary cell products or any component of atezolizumab formulation ➢History of idiopathic or secondary pulmonary fibrosis (history of radiation pneumonitis in the radiation field fibrosis is permitted), or evidence of active pneumonitis requiring a systemic treatment with 28 days before the planned start of study therapy ➢Major surgical procedure other than for diagnosis within 4 weeks prior to initiation of study treatment, or anticipation of need for a major surgical procedure during the course of the study ➢Severe infection within 4 weeks prior to initiation of study treatment, including, but not limited to, hospitalization for complications of infection, bacteremia, or severe pneumonia ➢Treatment with therapeutic oral or IV antibiotics within 2 weeks prior to the initiation of study treatment. Patients receiving prophylactic antibiotics (e.g., to prevent a urinary tract infection or chronic obstructive pulmonary disease exacerbation) are eligible for the study ➢Patients under chronic treatment with systemic corticoids or other immunosuppressive drugs (prednisone or prednisolone ≤10 mg/day is allowed) for a period of at least 4 weeks and whose treatment was not stopped 1 week prior to the start of the study treatment ➢Patient with intra-alveolar hemorrhage, pulmonary fibrosis or uncontrolled asthma, or chronic obstructive disease (COPD), defined as at least one hospitalization within 4 months prior to enrollment or as at least three exacerbations during the last year prior to enrollment ➢Patients requiring oxygen therapy ➢Patients with LEVF <40% ➢Hospitalization for cardiovascular or pulmonary disease within 4 weeks prior to enrollment ➢Receipt of a live, attenuated vaccine within 4 weeks prior to inclusion or anticipation that such a live, attenuated vaccine will be required during the study –Note: Patients must agree not to receive live, attenuated influenza vaccine (e.g., FluMist^®^) within 28 days prior to randomization, during treatment, or within 5 months following the last dose of atezolizumab ➢Inadequate hematology function: Lymphocyte count at baseline <800/mm^3^; neutrophil count <1,500/mm^3^; platelets <100,000/mm^3^; hemoglobin <9 g/dl ➢Inadequate hepatic function: bilirubin 2.5-fold ULN, AST/ALT 2.5-fold ULN, or 5-fold ULN with liver metastasis, international-normalized thromboplastin time ratio >1.5 ➢Inadequate renal function: MDRD CrCl <40 ml/min ➢Other inadequate laboratory values: serum albumin <30 g/L; troponin > ULN; BNP > ULN. ➢Active alcohol or drug abuse.

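### The skin-disease exception in Table 2 sets a minimum rash of 10% of body surface, so as written it admits more extensive disease and excludes limited disease.

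*Protocol article*

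**What the plan says.** The criterion is in Table 2 of the protocol article, under Section 2.3 (Patient Selection), among the exclusions headed as non-eligibility to treatment. The parent exclusion is broad: "Active or history of autoimmune disease or immune deficiency, including, but not limited to, myasthenia gravis" and a list of further diseases. Exceptions follow for hypothyroidism on replacement hormone, for controlled type 1 diabetes on insulin, and for skin disease. The skin exception covers "Patients with eczema, psoriasis, lichen simplex chronicus, or vitiligo with dermatologic manifestations only"; psoriatic arthritis is given as an example of what stays excluded. These patients "are eligible for the study provided that all of following conditions are met". Three conditions are listed:

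1. "Rash must cover ≥10% of body surface area".
2. "Disease is well controlled at baseline and requires only low-potency topical corticosteroids".
3. "No occurrence of acute exacerbations of the underlying condition requiring psoralen plus ultraviolet A radiation, methotrexate, retinoids", with biologics, oral calcineurin inhibitors and high-potency or oral corticosteroids also named, over the previous 12 months.

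Nowhere else does the article give another body-surface threshold or a reason for requiring a minimum extent of rash.

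**The concern.** An exception to an autoimmune exclusion exists to let in patients whose disease is too slight to matter. Conditions 2 and 3 do that, and so do the thyroid and diabetes exceptions. Condition 1 instead requires a minimum amount of disease. Because all three must hold, a patient with limited skin disease fails the exception and falls back under the general exclusion, while a patient with more widespread disease passes.

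What is at stake is mainly safety. Under Section 2.4 patients receive atezolizumab together with peptides emulsified in Montanide and injected subcutaneously. Section 2.5.7 says that the safety of this combination has not yet been studied in HPV-positive cancer, and for that reason sets up toxicity monitoring with a review if 7 or more of the first 14 patients have a relevant dose-limiting toxicity. A rule that favours wider autoimmune skin involvement works against that caution and could add immune-related skin events to the count. The rule also turns away suitable patients for no reason.

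**Working it through.** No sample size, error rate or power enters this point, so the check is one of logic.

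**Inputs, all from Table 2**

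- Parent rule: active or past autoimmune disease excludes the patient unless an exception applies.
- Exception: skin-only disease of one of the four listed types.
- Link between the conditions: all must be met, so they are joined by AND.
- Condition 1: rash at or above 10% of body surface.
- Condition 2: well controlled, low-potency topical steroid only.
- Condition 3: no exacerbation in 12 months that needed the listed therapies.

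**The rule as written**

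Eligible under the exception = skin-only disease AND (rash ≥10%) AND (condition 2) AND (condition 3).

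Take two patients who both have skin-only disease and both meet conditions 2 and 3. The 5% and 30% are illustrative.

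| Patient | Rash | Printed rule (≥10%) | Reversed rule (<10%) |
|---|---|---|---|
| A | 5% | 5 ≥ 10 is false: excluded | 5 < 10 is true: eligible |
| B | 30% | 30 ≥ 10 is true: eligible | 30 < 10 is false: excluded |

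The printed rule admits B and refuses A. The reversed rule does the opposite.

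**Direction of each condition**

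| Element | Restricts entry to |
|---|---|
| Thyroid exception | disease managed with replacement hormone |
| Diabetes exception | controlled disease on insulin |
| Skin-only requirement | no joint or systemic involvement |
| Condition 2 | controlled disease on minimal topical treatment |
| Condition 3 | no recent flare needing intensive treatment |
| Condition 1 | more extensive disease |

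Only condition 1 demands more disease. With <10% all the elements point the same way.

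**Could the symbol be a fault of text extraction?**

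Other inequality signs in the same table come through sensibly: "prednisone or prednisolone ≤10 mg/day is allowed" for steroids, "Lymphocyte count at baseline <800/mm^3" for blood counts, and a lower age limit of ≥18 with an upper limit of ≤75. An isolated extraction fault in this one line is therefore unlikely, although only the typeset article can rule it out completely.

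**The case against.** The strongest reply is that this is a journal article. Table 2 lists only the main criteria and refers to an Annex 5 that the article does not contain, so the text evidently comes from a fuller document. If that document has the opposite sign, the fault is a misprint and no patient was affected. This stands as a limit on what can be claimed about harm. It does not rescue the printed criterion, which the article states and does not merely omit.

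It is also fair to say that the three conditions are not logically incompatible. A patient can have 12% involvement, be well controlled on a low-potency steroid and have had no serious flare. The conflict is with the purpose of the exception, and "more extensive" must be read as skin area, not as uncontrolled disease.

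The exposure is bounded as well. Anyone admitted must meet conditions 2 and 3, must not have had active autoimmune disease treated systemically in the past 2 years, and can still be excluded for any medical condition that makes entry inappropriate. Refusing patients with limited disease costs accrual and does not cause harm.

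Finally, the article does not define dose-limiting toxicity or say whether skin events count, and it gives no prevalence. The number affected among 47 patients could be zero. An effect on the toxicity count is therefore possible but not shown.

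All of this limits the size of the consequence. None of it gives a reason for a minimum extent of rash.

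**Conclusion.** The concern holds. The body-surface condition is wrong as printed: it reverses the evident purpose of the exception and runs against the two conditions beside it. The error reaches every candidate with eczema, psoriasis, lichen simplex chronicus or vitiligo limited to the skin. Below 10% of body surface they are excluded; at 10% or above they are admitted if the other criteria are met. How many of the 47 planned patients this concerns cannot be worked out from the article.

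The conclusion about the text rests only on the wording of Table 2. The conclusion about patients assumes that sites work to the same sign. That <10% was intended is an inference from the companion conditions, although a strong one. The point concerns eligibility and safety; the Simon design (14 and 42 evaluable patients, one-sided 2.5% type I error, 90% power) is untouched. It should still be corrected, because it is an operative entry threshold in a trial of a combination with little safety experience. Leaving sites to guess the sign has no good outcome: a site that follows the text enrols the wrong patients, and a site that follows the intent departs from the written criterion.

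**What to change.** 1. Compare the sign with the approved full protocol and its annexes.
2. If the full protocol has <10%, publish a correction to Table 2 and confirm to sites that the protocol wording governs.
3. If the full protocol also has ≥10%, amend the condition to a rash covering less than 10% of body surface and notify sites at once.
4. In either case, list the patients with one of the four skin conditions who were included or refused under this criterion. Give the list of those included to the monitoring committee for its safety review.

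The cost is one character in Table 2 and a site notice, with an amendment if the protocol shares the error. Sample size, stopping boundaries and analysis populations do not change.
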